## 2.4 STUDY DESIGN AND DURATION

This is a randomized, active Control, safety/efficacy study. All eligible patients (antiretroviral naïve,) will be randomized (1:1) into two treatment groups:

1. Group A: will receive Raltegravir + Ritonavir-boosted Darunavir
2. Group B: will receive Tenofovir + Emtricitabine + Ritonavir-boosted Darunavir

For analysis, patients will also be stratified according to baseline viral load (VL <100,000 or ≥100,000) and baseline CD4 count (<200 or ≥200).

**Study Endpoints:**

Primary Outcome Measures:

## RADAR - Raltegravir And Darunavir Antiretroviral Regimen

- Time from randomization to virologic failure (HIV viral load of 1,000 copies/ml or greater at or after Week 16 and before Week 24, or two consecutive HIV viral load of 50 copies/ml or greater at or after Week 24)

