## 2. CORE PROTOCOL

### 2.1 OBJECTIVES AND HYPOTHESES

#### 2.1.1 Hypotheses

We hypothesize that the virologic efficacy (time to loss of virologic response) at 24 weeks will be at least as high following a regimen of Raltegravir + boosted Darunavir as with a regimen of Tenofovir + Emtricitabine + boosted Darunavir.

We further hypothesize that a regimen of Raltegravir + boosted Darunavir will not result in higher rates of adverse events at 24 weeks than a regimen of Tenofovir + Emtricitabine + boosted Darunavir.

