#### 2.1.2 Primary Objective

The primary objective is to determine whether a regimen of Raltegravir + Ritonavir-boosted Darunavir achieves a comparable virologic efficacy (TLOVR) at 24 weeks to Tenofovir + Emtricitabine + Ritonavir-boosted Darunavir

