## 2.5 LIST OF SAFETY MEASUREMENTS

Safety data of serious adverse experiences and drug-related adverse experiences that result in Grade 3 or above laboratory toxicity, lead to treatment interruption, or discontinuation will be collected on case report forms. The laboratory safety assessments should include a chemistry evaluation with serum creatinine, liver function tests, complete blood count and a lipid profile. Additional laboratory assessments would be performed per standard of care at the investigator's discretion. In addition, all patients that experience virological failure or who discontinue from the study early should have the 14-day post-therapy follow-up visit noted on the study flow chart (Section 1.6)

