## 2.6 DATA ANALYSIS SUMMARY

The primary analysis of efficacy and safety will be based upon the All Patients As Treated (APaT) approach, which includes all patients who received one or more doses of the test drug therapy. All patients who take study medication will be included in the analysis of safety and tolerability. Only those adverse experiences that occur while on study therapy or within 14 days after discontinuation of study therapy will be included in the analysis.

This is an estimation study. The primary endpoint is the comparison of the efficacy of the test regimen (Raltegravir + Darunavir) to Tenofovir + Emtricitabine + Darunavir. The mean effects of the test regimen (Raltegravir + Darunavir) will be compared to comparator regimen.

The analysis will be time to loss of virologic response (TLOVR) [12]. This analysis defines responders as subjects maintaining a minimum of two sequential HIV viral load <50 through the scheduled visits without intervening replicated rebounds or treatment discontinuations.

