## 3.4 Data Analysis

The primary analysis of efficacy and safety will be based upon the All Patients As Treated (APaT) approach which includes all patients who received one or more doses of the test drug therapy.

The primary endpoint is the comparison of the efficacy of the test regimen (Raltegravir + Darunavir) to Tenofovir + Emtricitabine + Darunavir. The mean effects of the test regimen (Raltegravir + Darunavir) will be compared to comparator regimen.

The analysis will be time to loss of virologic response (TLOVR) [12]. This analysis defines responders as subjects maintaining a minimum of two sequential HIV viral load <50 c/mL through the scheduled visits without intervening replicated rebounds or treatment discontinuations.

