**IRB Approved**

**06/24/13**

[figure not shown]

Logistic regression analysis will be used to analyze outcome data to determine the difference between the two regimens. With 40 patients enrolled in each arm, the study has 80% power to rule out a 15% difference in efficacy between the two regimens. This assumes a true response rate of 85% for both treatment groups.

The reasons for failure at week 48 should be the primary reason for the earliest treatment failure. For any visit, subjects who have achieved confirmed virologic success (two consecutive visits with HIV viral load < 50 copies/mL) will be considered successes. All others should be classified into the other appropriate categories listed in Table 2. All events occurring in the window should be considered events for that visit.

All patients who take study medication will be included in the analysis of safety and tolerability. Only those adverse experiences that occur while on study therapy, or within 14 days after discontinuation of study therapy will be included in the analysis.

For assessment of safety and tolerability, counts and percentages of patients with clinical or laboratory adverse experiences of the following type will be tabulated (1) serious adverse experience, (2) drug-related adverse experiences that result in grade 3 or above laboratory toxicity; (3) drug related adverse experiences that lead to treatment interruption; (4) drug related adverse experiences leading to discontinuation.

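### Section 2.4 scores primary failure on one unconfirmed Week 16 viral load, while the TLOVR objective and analysis count only replicated rebounds, so a patient kept on drug can be both a failure and a responder

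*Protocol*

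**What the plan says.** Under "Primary Outcome Measures" in Section 2.4, the protocol lists one item: time from randomization to virologic failure. Failure has two limbs. The first is "HIV viral load of 1,000 copies/ml or greater at or after Week 16 and before Week 24". The second asks for two consecutive values of 50 copies/ml or more from Week 24 on. The requirement for two values belongs to the second limb only.

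Elsewhere the primary efficacy measure is TLOVR:

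- Section 2.1.1 frames the hypothesis as "virologic efficacy (time to loss of virologic response) at 24 weeks".
- Section 2.1.2 asks whether the test regimen "achieves a comparable virologic efficacy (TLOVR) at 24 weeks".
- Section 3.4 states "The analysis will be time to loss of virologic response (TLOVR" as the analysis. Sections 2.6 and 3.4 define a responder in the same way: at least two sequential values below 50, "without intervening replicated rebounds or treatment discontinuations".
- Section 3.4 adds that at any visit a patient with confirmed success, meaning "two consecutive visits with HIV viral load < 50 copies/mL", counts as a success.

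The visit schedule (Sections 1.6 and 2.4.2) places viral loads at Weeks 2, 4, 8, 16, 24, 32, 40 and 48.

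**The concern.** The protocol states two rules for one primary endpoint, and they treat an isolated high value differently. Section 2.4 counts it as a terminal event at Week 16. TLOVR ignores it unless the next value repeats it. Nothing in the protocol ranks one rule above the other.

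What is at stake is whether the primary result is fixed in advance. Allocation is open-label (Section 2.4.2), so if the rule is still unsettled when outcomes are reviewed, it could be chosen with the results in view. With 40 patients per arm, a few patients scored differently would show in the estimate.

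**Working it through.** The protocol gives no figure of its own for this conflict, so the check is a side-by-side reading of the rules, followed by one line of arithmetic.

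**Step 1: which visits can trigger the first limb.** The window runs from Week 16 to before Week 24. Of the scheduled visits, only Week 16 lies in it. No repeat test is specified, although standard of care would allow one. On schedule, then, the first limb is decided by one measurement.

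**Step 2: one patient under both rules.** The patient stays on study drug throughout.

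| Visit | Viral load (copies/ml) | Section 2.4 rule | TLOVR rule (2.6, 3.4) |
|---|---|---|---|
| Week 4 | below 50 | outside both windows | first value below 50 |
| Week 8 | below 50 | outside both windows | second sequential value; response confirmed |
| Week 16 | 1,000 or more | first limb met: failure | possible rebound, not yet replicated |
| Week 24 | below 50 | already a failure | rebound not replicated; responder |

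The example does not depend on how TLOVR treats a first value below 50 at Week 24, because response was confirmed at Week 8 and the rebound was refuted by the Week 24 visit.

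**Step 3: the same patient if therapy is stopped after Week 16.** Section 2.4 still records failure. TLOVR now also records failure, through treatment discontinuation. The two rules agree, so the conflict is confined to patients who continue.

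**Step 4: size per patient.** Inputs are 40 patients per arm and a difference of 15 points to be ruled out (Sections 2.6 and 3.4).

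- One patient scored differently: 1/40 = 2.5 points in that arm.
- Relative to the limit: 2.5/15 = one sixth.

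The protocol gives no basis for the number of such patients. Purely as an assumption, 0, 1, 2 or 4 in one arm only would make the two definitions disagree on the between-arm difference by 0, 2.5, 5 or 10 points. The same number in both arms would leave the difference unchanged.

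**The case against.** **The weight of the text favours TLOVR.** The hypothesis, the objective and both analysis sections name it, and Section 2.4 stands alone. An analyst who used the Section 2.4 rule would be going against four places in the protocol. This stands, and it points to which rule to keep. It does not remove the conflict, because Section 2.4 is where the primary outcome is formally listed and it is not labelled secondary or supportive.

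**Failure may end therapy anyway.** Section 2.5 says that "all patients that experience virological failure or who discontinue from the study early should have the 14-day post-therapy follow-up visit", and Table 2 has a category for drug change due to virologic failure. If every patient with a high Week 16 value were switched, the two rules would agree. This also stands as a limit on the finding. But both places foresee a change of therapy without ordering it, and Section 3.2.3.5 does not name virologic failure as a reason to discontinue.

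**A statistical analysis plan could settle it.** It could, but only by overriding one of two stated definitions. This is a contradiction in the text, not a detail left for later.

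**This is a pilot estimation study (Section 1.4).** That tempers the seriousness, but an estimate still needs one definition.

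**Stronger readings that the documents do not support:**

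- A reader might infer that the conflict favours one regimen. Nothing in the protocol indicates which arm would have more isolated high values.
- A reader might infer a loss of power. That would need counts of affected patients, which the protocol does not give.
- A reader might add the slow responder who is at 50 or more at Week 24 and below 50 from Week 32. That case contrasts no failure so far with no response so far. It hinges on closing TLOVR at Week 24, which Sections 2.6 and 3.4 do not state, and by Week 48 Section 3.4 would call the patient a success. The point does not rest on it.

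**Conclusion.** The inconsistency is real but narrow. The first limb of the primary outcome in Section 2.4 contradicts the TLOVR rule in the hypothesis, objective and analysis for a patient who has confirmed suppression, a single value of 1,000 or more at Week 16, suppression again at Week 24, and no interruption of study drug. Such a patient is a primary failure and a primary responder at once.

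The size is 2.5 points in an arm per affected patient, one sixth of the 15-point limit, assuming the planned 40 per arm are analysed. The number affected is unknown and may be zero. The conclusion assumes that TLOVR is read at Week 24, as the hypothesis and objective say. It does not depend on the protocol's power figure. It should be corrected because the correction is cheap and leaves a single primary definition.

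**What to change.** In Section 2.4, replace the primary outcome with TLOVR response at Week 24 and state the rule there, because Section 2.6 names no week. Suggested content:

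- Response requires two consecutive viral loads below 50 copies/ml, with no replicated rebound and no treatment discontinuation up to Week 24.
- The scheduled Week 32 value is used to confirm a first value below 50, or a first rebound, seen at Week 24.

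Move time to virologic failure to the secondary outcomes, preferably with a confirmed first limb: two consecutive values of 1,000 copies/ml or more, the first at or after Week 16 and before Week 24. The example patient is then a responder on the primary outcome and not a failure on the secondary one.

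The cost is a text edit. No visits or tests are added, since viral loads are already scheduled at Weeks 16, 24 and 32. The Week 24 result would have to wait eight weeks (32 − 24) for patients whose status needs the Week 32 value. The definition should be fixed before outcomes are compared by arm.

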### Secondary Outcome Measures:

- Percentage of patients with serious adverse experience
- Percentage of patients with drug-related adverse experiences that result in grade 3 or above laboratory toxicity
- Percentage of patients with drug related adverse experiences that lead to treatment interruption
- Time from treatment dispensation to the first development of a Grade 3 or 4 sign, symptom, or laboratory abnormality that is at least one grade higher than at baseline
- Percentage of patients with HIV viral load levels less than 50 copies/ml at 24 and 48 weeks.
- Median CD4 count at 24 and 48 weeks and at virologic failure
- Median change in limb fat by DEXA at week 48
- Percentage of patients with occurrence of fasting hypertriglyceridemia (TG >400) or hypercholesterolemia (TC >240) at week 48
- HIV-1 drug resistance patterns at baseline and at time of virologic failure

For assessment of safety and tolerability, counts and percentages of patients with clinical or laboratory adverse experiences of the following type will be tabulated (1) serious adverse experience, (2) drug-related adverse experiences that result in grade 3 or above laboratory toxicity; (3) drug related adverse experiences that lead to treatment interruption; (4) drug related adverse experiences leading to discontinuation.

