# RADAR - Raltegravir And Darunavir Antiretroviral Regimen

## 1.6. STUDY FLOW CHART

| TRIAL PERIOD                            |            | SCREENING |          |          |          | TREATMENT |           |           |           |           |     |
|-----------------------------------------|------------|-----------|----------|----------|----------|-----------|-----------|-----------|-----------|-----------|-----|
| Week*                                   | (-4 to -3) | 0         | 2        | 4        | 8        | 16        | 24        | 32        | 40        | 48        | EOT |
| Day                                     | (-28)      | 0         | (14+/-2) | (28+/-2) | (56+/-4) | (112+/-4) | (168+/-4) | (224+/-4) | (280+/-4) | (336+/-4) |     |
| Visit                                   | 1          | 2         | 3        | 4        | 5        | 6         | 7         | 8         | 9         | 10        | 11  |
| Informed Consent                        | X          |           |          |          |          |           |           |           |           |           |     |
| Medical History and Baseline Conditions | X          |           |          |          |          |           |           |           |           |           |     |
| Physical Examination                    | X          | X         | X        | X        | X        | X         | X         | X         | X         | X         | X   |
| Weight and BMI Calculation              | X          | X         |          |          | X        | X         | X         | X         | X         | X         | X   |
| Eligibility Criteria                    | X          | X         |          |          |          |           |           |           |           |           |     |
| CBC                                     | X          | X         | X        | X        | X        | X         | X         | X         | X         | X         | X   |
| Metabolic Profile                       | X          | X         | X        | X        | X        | X         | X         | X         | X         | X         | X   |
| Viral Load                              | X          | X         | X        | X        | X        | X         | X         | X         | X         | X         | X   |
| CD4+ and CD8+ Cell Counts               | X          | X         | X        | X        | X        | X         | X         | X         | X         | X         | X   |

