#### 2.1.3 Secondary Objectives

- a. Determine whether Raltegravir + Ritonavir-boosted Darunavir at 48 weeks is associated with a median change in CD4 count from baseline comparable to Tenofovir + Emtricitabine + boosted Darunavir
- b. Compare the lipid profiles of patients receiving Raltegravir + Ritonavir-boosted Darunavir with those receiving Tenofovir + Emtricitabine + boosted Darunavir at week 48
- c. Determine changes in lipoprotein particles profile, as defined by their apolipoprotein composition and lipoprotein particle size distribution, (LDL subtypes 1 through 7 and HDL subtypes), in both treatment arm at weeks 16, 32 and 48.
- d. Determine any changes from baseline to week 48, in insulin resistance by homeostasis model assessment (HOMA-IR) derived from fasting plasma glucose and insulin levels
- e. Determine any changes in percent of body fat, lean body mass, and bone density on whole body DEXA scans between baseline and week 48.

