### Exploratory analyses

- Median change from baseline in components of lipid panel at Weeks 48
- Changes in glucose tolerance as measured by the HOMA-IR
- Changes in lipoprotein profile and LDL and HDL particle size and distribution
- Virologic and immunologic response, safety, and tolerability by race/ethnicity, age, gender, and hepatitis C coinfection
- Occurrence of targeted clinical events, including death, AIDS-defining illness, and HIV-1 related events (including the CDC Category B diseases)

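### The CD4 objective is a median change from baseline, but the only CD4 outcome listed is the raw median count, and baseline CD4 enters only as a two-level stratum

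*Protocol*

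**What the plan says.** The first secondary objective (Protocol, Section 2.1.3, item a) is to determine whether the raltegravir arm at 48 weeks "is associated with a median change in CD4 count from baseline comparable to Tenofovir + Emtricitabine + boosted Darunavir".

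The Secondary Outcome Measures in Section 2.4 contain one CD4 entry: "Median CD4 count at 24 and 48 weeks and at virologic failure". The exploratory list in the same section mentions immunologic response by subgroup but does not define it as a CD4 change.

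Two other continuous outcomes in those lists are written as changes: "Median change in limb fat by DEXA at week 48" (secondary) and "Median change from baseline in components of lipid panel at Weeks 48" (exploratory).

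On baseline CD4, Section 2.4 says: "For analysis, patients will also be stratified according to baseline viral load (VL <100,000 or ≥100,000) and baseline CD4 count (<200 or ≥200". This concerns analysis. Allocation is described only as 1:1 (Sections 2.4 and 3.2.3.3), and the eligibility criteria set no CD4 limit.

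The flow chart in Section 1.6 has a row for "CD4+ and CD8+ Cell Counts" marked at screening, week 0 and every later visit, so each patient's change can be derived.

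**The concern.** The objective and the outcome name different quantities. A median of within-patient changes is not, in general, the difference between the median at week 48 and the median at baseline. Comparing arm medians of the week-48 count therefore does not estimate what Section 2.1.3(a) asks for. An analysis plan could choose the model, but it would still face two protocol definitions of the CD4 endpoint. In an open-label trial (Section 2.4.2), leaving the choice between level and change open is undesirable.

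Precision is the second matter. With no CD4 entry limit, baseline counts may vary widely. With 40 per arm and no described stratification of the allocation, the arms can differ at baseline by chance, and a comparison of week-48 counts carries that difference in proportion to the correlation between the two time points. The stated CD4 split is coarse, and Section 2.4 does not say to which outcomes it applies.

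**Working it through.** **No plan figure to reproduce.** The protocol gives no sample size, SD, correlation or margin for CD4. Its one power statement (Section 3.4) concerns virologic response.

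**Step 1: text comparison**

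| Source | Quantity | Time |
|---|---|---|
| Section 2.1.3(a) | median change from baseline | week 48 |
| Section 2.4, Secondary Outcome Measures | median level | weeks 24 and 48, and at virologic failure |
| Section 2.4, limb fat | median change | week 48 |
| Section 2.4, lipid panel | median change from baseline | week 48 |

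The CD4 objective has no matching outcome, although the same section writes change explicitly elsewhere.

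**Step 2: chance imbalance.** Input: 40 per arm (Section 3.4). In units of the baseline SD, the standard error of the between-arm difference in mean baseline CD4 is √(2/40) = 0.22, a 95% range of about ±1.96 × 0.2236 = ±0.44 SD.

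Splitting a normal variable at its median captures 2/π = 0.64 of its variance. If 200 lies near the median, the imbalance left within strata has a standard error of about √(1 − 0.64) × 0.22 = 0.6 × 0.22 = 0.13 SD. The split reduces the imbalance but does not remove it. The assumption about 200 is not unreasonable: the only CD4 median in the protocol is 228 cells/mm³, from the cited once-daily darunavir trial in treatment-naïve patients (Section 3.1).

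**Step 3: variance of the arm comparison.** Let ρ be the baseline-to-week-48 correlation. It is not in the document and is assumed here. With equal SDs at both times, and relative to a wholly unadjusted level (= 1):

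- unadjusted change: 2(1 − ρ)
- level stratified at 200: 1 − 0.64ρ²
- baseline-adjusted (ANCOVA): 1 − ρ²

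The number per arm that the adjusted analysis acts like is 40/(1 − ρ²) against the unadjusted level, and 40(1 − 0.64ρ²)/(1 − ρ²) against the stratified level.

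| ρ | Change | Stratified level | Adjusted | n per arm vs unadjusted | n per arm vs stratified |
|---|---|---|---|---|---|
| 0.3 | 1.40 | 0.94 | 0.91 | 44 | 41 |
| 0.4 | 1.20 | 0.90 | 0.84 | 48 | 43 |
| 0.5 | 1.00 | 0.84 | 0.75 | 53 | 45 |
| 0.6 | 0.80 | 0.77 | 0.64 | 63 | 48 |
| 0.7 | 0.60 | 0.69 | 0.51 | 78 | 54 |
| 0.8 | 0.40 | 0.59 | 0.36 | 111 | 66 |

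**Step 4: does this carry over to medians?** The formulas are for means. A simulation with normal data, 40 per arm and 20,000 runs gave the variance of the difference in medians, change relative to level, as 0.99, 0.60 and 0.40 at ρ = 0.5, 0.7 and 0.8. These match the change column.

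**Reading.** An unadjusted change is less precise than the raw level when ρ is below 0.5, and it does not beat the stratified level even at 0.6 (0.80 against 0.77). Adjustment for continuous baseline is the smallest figure in every row. Relabelling the outcome as change would settle the contradiction, but it would not by itself guarantee better precision.

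**The case against.** The strongest reply is that this is a wording slip in one secondary endpoint of an 80-patient pilot. The objective already names the change, CD4 is measured at week 0 and week 48, and the choice of model belongs to an analysis plan that is not at hand. Much of that is fair. The absence of a CD4 model is not a fault of the protocol, and ANCOVA is offered here as part of the remedy. The mismatch itself stands, because it lies between two statements in the protocol.

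Four stronger readings are tempting, and the documents do not support them.

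- *Baseline CD4 is discarded.* It is not. The stratification sentence in Section 2.4 continues past viral load to baseline CD4 at 200. Baseline is coarsened.
- *The CD4 objective cannot be answered.* Under 1:1 randomisation, the expected between-arm difference in mean week-48 counts equals that in mean changes, so levels still bear on comparability. They do not estimate the median change.
- *The loss is that between 40 and 53 to 111 patients per arm.* That compares adjustment with a level analysed with no use of baseline at all. Against the stated two-level stratification the range is 45 to 66.
- *CD4 at failure is an arm comparison resting on about 6 patients per arm.* The protocol does not say this summary is compared between arms. The 6 would be 15% of 40, but the 85% in Section 3.4 is response under TLOVR, and non-response there includes treatment discontinuation. Virologic failure in Section 2.4 is defined by viral load alone, so the two counts are not the same.

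**Conclusion.** The point holds as an internal contradiction. Section 2.1.3(a) specifies the median CD4 change from baseline at week 48, Section 2.4 lists only the median CD4 count, and no listed outcome estimates the stated quantity. This part needs no assumption.

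The precision part is conditional. At 40 per arm the chance baseline imbalance has a standard error of 0.22 SD, and a split at 200 removes only part of it. For assumed correlations of 0.5 to 0.8, equal SDs, normal data and 200 near the median, continuous adjustment acts like about 45 to 66 per arm relative to the stratified analysis. At correlations of 0.3 to 0.4 the gain is small (41 to 43). The stratified comparator also assumes that the Section 2.4 strata are applied to CD4, which the protocol does not say.

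The matter concerns a secondary endpoint and leaves the primary analysis untouched. It is worth correcting because the correction is nearly free.

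**What to change.** In the Secondary Outcome Measures (Section 2.4), replace the CD4 entry with *change from baseline in CD4 count at weeks 24 and 48*, so that it matches Section 2.1.3(a).

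State that arms are compared with baseline CD4 as a continuous covariate, by ANCOVA or by quantile regression if the median is kept, and that the between-arm difference is reported with a 95% CI. The adjustment should accompany the change of outcome, since an unadjusted change score can be less precise than the level.

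Keep CD4 at virologic failure as a separate line, labelled descriptive.

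Cost: one or two lines in the outcome list and a routine model. The measurements are already scheduled, so no visits, samples or patients are added.

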### 1.4. SUMMARY OF STUDY DESIGN

This is a randomized, active control, safety/efficacy pilot estimation study. Eighty patients will be randomized 1:1 into two different treatment groups:

1. Group A: will receive Raltegravir + Ritonavir-boosted Darunavir
2. Group B: will receive Tenofovir + Emtricitabine + Ritonavir-boosted Darunavir

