**IRB Approved**

**06/24/13**

[figure not shown]

Logistic regression analysis will be used to analyze outcome data to determine the difference between the two regimens. With 40 patients enrolled in each arm, the study has 80% power to rule out a 15% difference in efficacy between the two regimens. This assumes a true response rate of 85% for both treatment groups.

For assessment of safety and tolerability, counts and percentages of patients with clinical or laboratory adverse experiences of the following type will be tabulated: (1) serious adverse experience; (2) drug-related adverse experiences that result in grade 3 or above laboratory toxicity; (3) drug related adverse experiences that lead to treatment interruption; (4) drug related adverse experiences leading to discontinuation.

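### The only secondary lipid outcome is a TG/TC threshold share at week 48, which matches objective 2.1.3b poorly and is less precise than the continuous change left as exploratory

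*Protocol*

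**What the plan says.** Section 2.1.3, objective b: "Compare the lipid profiles of patients receiving Raltegravir + Ritonavir-boosted Darunavir with those receiving Tenofovir + Emtricitabine + boosted Darunavir at week 48".

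Section 2.4, Secondary Outcome Measures, has one lipid item: "Percentage of patients with occurrence of fasting hypertriglyceridemia (TG >400) or hypercholesterolemia (TC >240) at week 48". It sets no baseline condition, and the eligibility criteria in sections 2.2 and 2.3 place no limit on lipids at entry.

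Section 2.4, Exploratory analyses, lists "Median change from baseline in components of lipid panel at Weeks 48". HOMA-IR and lipoprotein particle changes are in the same exploratory list, although section 2.1.3 names them as secondary objectives d and c.

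The flow chart (section 1.6) schedules a fasting lipid panel at screening, week 0 and every later visit. On size and framework, the protocol states "Eighty patients will be randomized 1:1 into two different treatment groups" and "This is an estimation study".

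**The concern.** The objective and the outcome meant to answer it do not line up. A lipid profile has several components. The secondary outcome covers two of them, each reduced to yes or no at a high cut. The measure closest to the objective sits one tier lower.

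The baseline is also left out. A patient who enters with total cholesterol above 240 and stays there counts in the same way as one who crosses the cut on treatment. Neighbouring items in the same list are built differently: the grade 3 or 4 outcome requires worsening over baseline, and limb fat is a change score.

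Lipids matter in this trial. Section 1.3 argues from a protease inhibitor with a better metabolic profile, and section 3.1 reports more hypertriglyceridemia in earlier NRTI-free arms. If the secondary tier determines what is reported as the answer to objective b, that answer will rest on a coarse count in a small trial.

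**Working it through.** **The plan's own figure.** There is none for lipids. The only power statement is "With 40 patients enrolled in each arm, the study has 80% power to rule out a 15% difference in efficacy between the two regimens" (sections 2.6 and 3.4), which concerns virologic response and is not used here.

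**Inputs.** From the protocol: 40 per arm and the threshold form of the outcome. Assumed, because the protocol gives nothing: one normally distributed lipid value, a between-arm shift d = 0.5 SD, a share p0 above the cut in the lower arm of 5% to 50%, a baseline to week-48 correlation r of 0.5 to 0.7, a two-sided 5% test, and no missing week-48 values.

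**Continuous comparison.** The noncentrality is d × √(n/2) = 0.5 × √20 = 2.236. With 78 degrees of freedom the t-test has power 59.8%.

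**Baseline-adjusted comparison (ANCOVA).** The residual SD shrinks by √(1 − r²), so the effective shift is 0.5/√(1 − r²):
- r = 0.5: 0.577, power 72%
- r = 0.6: 0.625, power 79%
- r = 0.7: 0.700, power 87%

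**Threshold comparison.** The cut is c = Φ⁻¹(1 − p0), and the higher arm has p1 = 1 − Φ(c − 0.5). Chi-square power is Φ[(p1 − p0 − 1.96·s0)/s1], with s0 = √[2p̄(1 − p̄)/40] and s1 = √[(p0(1 − p0) + p1(1 − p1))/40], where p̄ is the mean of p0 and p1.

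Example at p0 = 10%: c = 1.282, p1 = 21.7%, s0 = 0.0817, s1 = 0.0806. Power = Φ[(0.1172 − 0.1601)/0.0806] = Φ(−0.53) = 29.7%.

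The last column is the share of information about the shift that the cut keeps, φ(c)²/[p0(1 − p0)].

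| p0 | p1 | Chi-square power | Fisher power | Chi-square as share of 59.8% | Information kept |
|---|---|---|---|---|---|
| 5% | 12.6% | 22.2% | 10.2% | 37% | 22% |
| 10% | 21.7% | 29.7% | 21.5% | 50% | 34% |
| 20% | 36.6% | 37.7% | 29.5% | 63% | 49% |
| 30% | 49.0% | 41.1% | 33.5% | 69% | 58% |
| 50% | 69.1% | 41.3% | 33.9% | 69% | 64% |

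**In estimation terms.** Keeping 22% to 64% of the information is like using about 9 to 25 of the 40 patients per arm (40 × 0.224 = 9.0; 40 × 0.637 = 25.5). An interval for the shift is then about 2.1 to 1.25 times as wide (1/√0.224; 1/√0.637).

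**Concrete case for total cholesterol alone.** Assume SD 40, lower-arm mean 180 and a difference of 20 mg/dL. The shares above 240 are 6.7% and 15.9%. By normal approximation the threshold has 25% power, the week-48 value 61%, and the adjusted value at r = 0.6 80%.

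**Limits of the check.** The outcome names two analytes. If they are combined into one event, the share above a cut is higher than for either alone, which moves down the table towards a smaller loss. The exploratory item is a median change. A median test has efficiency of about 0.64 under normality, so its advantage over the threshold is smaller than the t-test comparison shows.

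**The case against.** The strongest reply is that nothing is lost. The lipid panel is drawn at every visit, the continuous change is already listed, and an estimation study with no error rate or testing order for secondary outcomes draws no different inference when an item moves up a tier. Objective b speaks of lipid profiles at week 48, not of change. A rate of marked elevation is a legitimate clinical readout and fits the evidence cited in section 3.1. Randomisation balances baseline dyslipidaemia in expectation, so counting it adds noise and not bias. Whether an occurrence means new onset may be defined in the analysis plan.

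Much of this stands. The continuous information is demoted, not discarded; the week-48 visit is the right one; and the threshold share deserves to be reported. What does not fall away is the mismatch: a count on two analytes does not describe a lipid profile, and tier decides what is presented as the answer to objective b. The estimation label does not help either, since a coarser outcome gives a wider estimate whether or not a test is done.

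Two stronger readings are tempting. A reader might infer that the threshold loses most of the power. The documents cannot support that as a general statement, because they give no event rate. Against the unadjusted continuous test, more than half is clearly lost only when about 5% or fewer exceed the cut; at 10% it is about half, and at 20% to 50% roughly a third. A reader might also infer that the whole metabolic question is compromised. It is not: limb fat change is already a continuous secondary outcome, so the precision point concerns lipids only.

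**Conclusion.** The point holds as a mismatch of outcome and tier with a real cost in precision. For objective b, the secondary list offers only a two-analyte threshold share with no baseline condition; objectives c and d have no secondary outcome at all, and appear only as exploratory.

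The threshold outcome was less powerful in every scenario run. At an assumed 0.5 SD shift, its chi-square power of 22% to 41% compares with 60% unadjusted and 72% to 87% baseline-adjusted. The direction is secure; the size rests on the assumed shift, share above the cut, correlation, normality and complete week-48 data. The primary virologic analysis is not affected.

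**What to change.** 1. Make the secondary lipid outcome the week-48 fasting total cholesterol, LDL, HDL and log triglycerides (or their change from baseline), compared between arms by ANCOVA on the baseline value, with estimates and confidence intervals.
2. Keep the TG and TC thresholds as a supportive count. Report them both as worded now and as new occurrences among patients below the cut at baseline. State whether the two analytes form one event or two.
3. Align section 2.1.3 with the outcome lists in section 2.4 for objectives b, c and d: either move lipoproteins and HOMA-IR into the secondary outcomes or relabel those objectives as exploratory.

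The cost is outcome-list wording and a standard model on data already scheduled; no visits, samples or patients are added. The downside is that the threshold share, which is easy to read clinically, becomes supportive.
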